### Design

This protocol adheres to the guidance of the Standard Protocol Items: Recommendations for Interventional Trials (SPIRIT) statement for reporting randomized clinical trials [42]. The design is a single-center, parallel group, randomized controlled trial comparing prenatal MBSR as add on to usual care (UC) with usual care alone. Participants are randomized in a 1:1 ratio to an intervention group or a waitlist control group receiving care as usual. Participants in the waitlist control group are offered participation in an equivalent MBSR program for mother and baby after the follow-up period. An outline of the study timeline is shown in Table 1.

**Table 1 Tab1:** Participant timeline

Timeline	Event
First consultation	Interest in study participation and preliminary eligibility is established at first consultation at the obstetric outpatient clinic (around 18 weeks gestation), and written information is emailed to possible participants.
− 2 weeks	Interview to determine eligibility and participation within two weeks from first consultation.
− 3 weeks	Motivational interviewing (MI)
	Baseline questionnaire
0	Randomization
+ 2 weeks	Start of the intervention (9 weeks)
T1 (1½ months)	1½ months post-randomization: second and intermediate assessment
T2 (3 months)	3 months post-randomization: Third assessment
T3 (6 months)	6 months post-randomization: Fourth assessment
T4 (9 months)	9 months post-randomization: Fifth and final assessment

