### Intervention: the prenatal MBSR program

The prenatal MBSR program is an adaptation of MBSR in order to fit into a clinical context. Importantly, the essential “warp” elements characterizing MBSR were maintained [43]. The adaptation process is described in detail in [name] et al. [41]. In brief, the prenatal MBSR program include nine weekly two-hour classes with a maximum of 15 participants per group. The program is delivered in a combination between physical attendance (class 1, 4 and 9) and live-online teaching. The intention of combining physical attendance with live-online teaching is to reduce travelling and ensure attendance while still providing a good starting point for establishing a learning environment and a sense of community in the group. Pregnancy and motherhood are a natural focus throughout the program, e.g. sitting meditations include periods sitting with one hand on the pregnant belly and the other hand on the heart. Yoga programs suitable for pregnancy was developed. The recommended time for daily mindfulness training between classes is 15 min a day with options for longer practice. This in order to make the course requirements manageable considering the psychosocial vulnerabilities of the women. Participants receive an email after each class summarizing key points from the training and instructions for home practice. Audio recordings with guided meditations and videos with the yoga programs for pregnancy are provided for home practice. Participants are asked to register the time they spent on formal mindfulness practice between classes. The data will be collected after the final class. Participation is registered for each class and participants are encouraged to notify the teacher in case of non-attendance. Participants will be contacted by phone in cases of absence from two successive classes or in cases where the teacher is not notified about non-attendance.

A certified MBSR teacher with a professional background in psychiatry (last author, [name]) teach the prenatal MBSR program. Three midwifes employed at the obstetric ambulatory clinic, who are training to become MBSR teachers, co-teach the prenatal MBSR program. Only one midwife at a time is a co-teacher for a group.

An online booster session is offered three months after finalizing the 9-week program where the new mothers are invited to bring their babies and thus making it an opportunity to practice being mindful with their baby.

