### Sample size

The primary outcome is change in mental well-being (WHO-5) from baseline to post-intervention. The aim is to include 240 psychosocially vulnerable pregnant women in the period from March 2022 and until the desired number has been reached. About 750 women are referred to the obstetric ambulatory clinic every year and the time span is therefore considered realistic. Out of 240 pregnant women, 168 (70%) is expected to complete the study based on the dropout rate in the feasibility trial [41]. With this sample size, a standard deviation of 15.6 (data from the feasibility trial) and a two-sided alpha of 5%, the study has 82% power to detect a difference of 7 on the WHO-5 between the two study groups, and 91% power to detect a difference of 8 on the WHO-5.

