### Randomization

The study will use the REDCap randomization module hosted by Aarhus University for the randomization procedure. To secure concealment, a data manager from Aarhus University, not otherwise involved in the study, programed the randomization algorithm. Enrollment and randomization is conducted by the responsible researcher, and takes place after the statement of consent has been signed and the first questionnaire has been filled in. Participants are randomized in a 1:1 ratio. Inclusion and thus randomization will take place consecutively.

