### Statistical analysis plan

Statistical analyses will be performed using SPSS for Windows (version 28; IBM Corp, Armonk, NY) or Stata (version 16). Recruitment, participation and retention rates will be reported in a CONSORT flow diagram [58]. Analyses on the primary outcome will be conducted on the intent-to-treat population meaning all randomized participants with completed baseline assessments. Compliance is considered as participation in five or more of intervention-scheduled classes.

Baseline sociodemographic data will be presented by means of frequencies (percentages), medians (interquartile range), and means (SD), according to their level of measurement and statistical distribution.

Statistical analysis of primary outcome, mental wellbeing, will be performed using a repeated measurement model with systematic effects, randomization arm, time (baseline, 3, 6 and 9 months post-randomization), intervention (prenatal MBSR, waitlist control group), interaction between time and intervention, baseline values of: age, perceived stress and use of psychotropic drugs. The model will include random effects of person and “scheduled group”. The primary effect estimate is the mean difference in change since baseline between the intervention group and the control group at nine months post-randomization. The change from baseline at 3 and 6 months will also be reported. Equivalent models will analyze secondary outcomes, stress, anxiety and depression. The change from baseline to three months after randomization in maternal antenatal attachment will be analyzed in a model with the systematic effect of intervention, baseline mental wellbeing, perceived stress, age, number of children and random effect of “scheduled group”. Equivalent models will be used in the analysis of experience of childbirth. A per-protocol analysis of the primary outcome will be performed with three intervention levels: (1) attending five or more of intervention-scheduled sessions, (2) attending less than five of intervention scheduled sessions and (3) waitlist control group. No subgroup analyses is planned. Standard errors will be based on the bootstrap method, resampling persons.

The five measurement points allow to test whether changes in the proposed mediators, i.e. mindfulness and self-compassion, are associated with changes in the proposed outcomes. Structural equation modelling will be used for the statistical analyses of the proposed mechanisms [59].

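### The bootstrap of persons leaves out the within-class covariance in the MBSR arm; if class effects exist, the primary confidence interval is too narrow and type I error exceeds 5%

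*Protocol article*

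**What the plan says.** All points are from the protocol article.

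- **Delivery** (Intervention: the prenatal MBSR program): the program consists of "nine weekly two-hour classes with a maximum of 15 participants per group".
- **Controls** (Design): "Participants in the waitlist control group are offered participation in an equivalent MBSR program for mother and baby after the follow-up period". Up to nine months, therefore, only the MBSR arm is taught in classes.
- **Allocation** (Randomization): "Participants are randomized in a 1:1 ratio", individually and consecutively.
- **Primary model** (Statistical analysis plan): a repeated-measures model with baseline, 3, 6 and 9 months as outcome times. "The model will include random effects of person and" scheduled group. No group-by-time term is named, and scheduled group is not defined.
- **Primary contrast** (same section): "The primary effect estimate is the mean difference in change since baseline between the intervention group and the control group at nine months post-randomization".
- **Standard errors** (same section): "Standard errors will be based on the bootstrap method, resampling persons". The sentence closes the paragraph that also covers the secondary outcomes, antenatal attachment, childbirth experience and the per-protocol analysis.
- **Sample size**: "Out of 240 pregnant women, 168 (70%) is expected to complete the study based on the dropout rate in the feasibility trial", with "a standard deviation of 15.6 (data from the feasibility trial) and a two-sided alpha of 5" percent. No allowance is made for classes.

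**The concern.** The section makes two choices that do not fit together. The random effect of scheduled group says that women in one group may be alike. The bootstrap then draws women one at a time, as if classmates were independent.

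Resampling persons does keep each woman's repeated visits together, so the correlation within a woman is handled. The correlation between women in one class is not.

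Any class effect on outcome arises after baseline and in the MBSR arm only. If it exists, the reported uncertainty of the primary contrast is too small, and the error favours a positive finding. The bootstrap sentence carries the same problem to the other analyses in its paragraph.

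**Working it through.** **Inputs.** From the article: 168 completers, so 84 per arm at 1:1; SD 15.6; two-sided 5%; at most 15 per class. Assumed: an ICC of 0 to 0.10 for the analysed quantity, and 8, 12 or 15 classes. Eight is the fewest possible for 120 women (120/15 = 8); 12 and 15 correspond to classes of 10 and 8. Completers per class are m = 84/8 = 10.5, 84/12 = 7 and 84/15 = 5.6.

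**1. The stated power.** SE = 15.6 × √(2/84) = 2.407. Power for a difference of 7 is Φ(7/2.407 − 1.96) = 82.8%, and for 8 it is 91.4%. With the noncentral t they are 82.4% and 91.1%. The stated 82% and 91% are reproduced without any clustering term.

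**2. What a person bootstrap omits.** The true variance of the MBSR mean is (σ²/84) × [1 + (m − 1) × ICC]. A person bootstrap estimates about σ²/84. Between-class variance is part of σ² and so does enter; the missing part is the covariance term (σ²/84) × (m − 1) × ICC. With unclustered controls,

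r = true SE / person-level SE = √{[2 + (m − 1) × ICC]/2}, and type I error = 2 × [1 − Φ(1.96/r)].

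Example with 8 classes and ICC 0.05: r = √[(2 + 9.5 × 0.05)/2] = √1.2375 = 1.112. The person-level SE is 1/1.112 = 0.90 of the true one, and 1.96/1.112 = 1.762 gives 7.8%.

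| ICC | 8 classes: r | type I | 12 classes: r | type I | 15 classes: r | type I |
|---|---|---|---|---|---|---|
| 0 | 1.000 | 5.0% | 1.000 | 5.0% | 1.000 | 5.0% |
| 0.01 | 1.023 | 5.6% | 1.015 | 5.3% | 1.011 | 5.3% |
| 0.02 | 1.046 | 6.1% | 1.030 | 5.7% | 1.023 | 5.5% |
| 0.05 | 1.112 | 7.8% | 1.072 | 6.8% | 1.056 | 6.3% |
| 0.10 | 1.214 | 10.7% | 1.140 | 8.6% | 1.109 | 7.7% |

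**3. Simulation.** In 4,000 null trials with 8 classes and 400 person resamples each, the mean bootstrap SE was 2.39, 2.39, 2.38 and 2.38 at ICC 0, 0.02, 0.05 and 0.10. The true SE was 2.35, 2.49, 2.68 and 2.92. The bootstrap SE does not respond to the ICC. Rejection rates were 5.4%, 6.7%, 8.4% and 11.3%. Larger simulations using the person-level SE directly gave 6.1% to 6.5%, 7.9% to 8.5% and 11.0% to 11.4% at the three non-zero ICCs. With 12 to 15 classes, simulation gave about 6%, 7% and 8 to 9%. The simulated rates lie slightly above the formula, partly because a normal critical value is used with an estimated SE; this also explains 5.4% at ICC 0.

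**4. Does the group intercept repair it?** A group effect that is the same at every visit, baseline included, drops out when baseline is subtracted. A class effect that begins after baseline does not. The model was fitted by REML to simulated data with class effects at 3, 6 and 9 months only (random person, time-constant random group, no baseline covariates). The model-based SE was 2.41 against a true 2.72 at ICC 0.05, and 2.45 against 3.04 at ICC 0.10. The result was the same whether groups were coded as MBSR classes only or across both arms.

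**5. A class-based SE.** With class means in the MBSR arm and Satterthwaite degrees of freedom, simulated type I error was 4.8% to 5.0% at every ICC tried.

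**The case against.** **The effect may be small.** One certified teacher leads the program, six of the nine classes are online, and home practice is individual. Teaching starts 2 weeks after randomization and lasts 9 weeks, so the nine-month outcome (about week 39) comes some 28 weeks after the last class. An online booster session falls in between. All this points to a low ICC, and classes may be smaller than 15. This stands: it limits the size, and no ICC in the article supports an unconditional claim that the interval is too narrow.

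**The random effect already deals with groups.** This fails. The article takes its standard errors from the bootstrap, not the model, and the intercept would not help the change contrast anyway. For antenatal attachment, analysed as a single change score, a class random effect could have carried the clustering into a model-based SE; the bootstrap overrides it.

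**Scheduled group may mean intake waves across both arms.** Possible, since it is undefined. A wave effect shared by both arms would cancel from the contrast, but an effect of the MBSR class would not.

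**A condensed article may leave details to a full plan.** True of the definition of scheduled group. It does not cover the resampling unit, which the article states outright.

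A reader might also infer three stronger things. One is that between-class variance never enters the bootstrap; it does, at person level, and only the covariance is lost. Another is that the group intercept cancels exactly; the check supports only that it largely does. The third is that the bootstrap must be abandoned; one that resamples classes is also valid with a small-sample correction.

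**Conclusion.** The concern holds in conditional form. The stated rule omits within-class covariance in the MBSR arm, and nothing else in the article corrects it. The direction is certain for any positive class effect on the nine-month change, a possibility that the plan's own random effect allows for. The size is not known. Under the assumptions above, type I error is about half a point too high at ICC 0.01, about 1 point at 0.02, 1.5 to 3.5 points at 0.05 and 3 to 6 points at 0.10, depending on the number of classes. At ICC 0 nothing is wrong. The documents do not show that type I error is in fact above 5%, nor that the power arithmetic is in error: the power reproduces and simply assumes independence.

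**What to change.** 1. Define scheduled group: MBSR classes only, or waves that include controls. Assign every woman in the MBSR arm to her scheduled class, attended or not, in line with intention to treat.
2. Replace the resampling of persons with one of these:
   - a partially nested mixed model with a class effect acting only in the MBSR arm and only at post-baseline visits, with Satterthwaite or Kenward-Roger degrees of freedom; or
   - a bootstrap that resamples whole classes in the MBSR arm and persons in the control arm, with a small-sample correction, since there may be only about 8 classes.
3. Apply the same rule to the secondary, attachment, childbirth and per-protocol analyses.

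This changes wording and code, not data collection, and should be settled before outcomes are analysed by arm.

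The cost is precision. With 8 classes, the 95% half-width rises from 1.96 × 2.407 = 4.72 to 4.94, 5.25 and 5.73 at ICC 0.02, 0.05 and 0.10. Power for a difference of 7, Φ[7/(2.407 × r) − 1.96], falls from 82.8% (stated as 82%) to 79.4%, 74.3% and 66.8%. With 12 to 15 classes it is about 81% at ICC 0.02 and 77% to 79% at 0.05. Small-sample degrees of freedom lower these a little further. If class effects exist, the loss is already in the design; the fix makes it visible.

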### Blinding

Group allocation will not be blinded since keeping participants blind to this type of intervention would not be possible.

### Scientific ethical considerations

Participation in a mindfulness-based program has not been associated with an increased incidence of harm when compared to no treatment [60]. The most common experiences of harm or adverse effects of meditation including mindfulness-meditation is anxiety, traumatic re-experiencing and emotional sensitivity [61]. However, childhood adversity has been associated with a higher frequency of adverse effects [61], which emphasize the need for trauma sensitivity in the present context. A psychiatrist with extensive clinical psychiatric experience will be teaching the prenatal MBSR program. If any adverse events should occur, the teacher has the relevant expertise to ensure participant safety or referral to relevant treatment elsewhere. The teacher and co-teacher are available for individual sessions between the program sessions if needed. Any side effects related to the intervention will be registered and published with the results of the study. The possible benefits of mindfulness training in pregnancy as described in earlier sections thus outweighs the potential side effects of the intervention. Moreover, there is a need for more evidence-based, non-pharmacological options for addressing prenatal mental healthcare needs in vulnerable groups for the benefit of both mother and baby. The adaptations made to the original MBSR program require more research in order to establish an evidence-base for the prenatal MBSR program, which is the aim of this study.

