## Methods

### Setting

The study is carried out at an obstetric ambulatory clinic at Copenhagen University Hospital, Hvidovre, which is the largest birthplace in Denmark with 7000 annual births. The obstetric ambulatory clinic has on average 750 referrals per year and is one of five ambulatory clinics in Denmark, which provide antenatal care for highly vulnerable pregnant women. Reasons for referral to the obstetric ambulatory clinic is a preconception history of one or more mental disorders irrespective of illness stage at the time of referral and/or complicating psychosocial vulnerabilities. Psychosocial vulnerabilities include, but not limited to, a history of childhood adversity, sexual assaults, present physical or psychological intimate partner violence, past or current substance abuse, current affective disorders or poor adaptation to pregnancy. In the majority of cases (> 60%) the reason for referral include a preconception history of one or more mental disorders. The purpose of the antenatal care as determined by the Danish Health Authority is to reduce the risk for obstetric complications and to promote a healthy pregnancy, including maternal antenatal attachment. Due to the complexity, the obstetric ambulatory clinic works multidisciplinary and include midwifes, physicians, social workers and psychologists. In Denmark, there is free and equal access to most healthcare services including hospitals, general practitioners and practicing specialists. General practitioners act as the gateway to all healthcare services.

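### Side effects are registered by relatedness to the intervention, so registered harms have no control-arm comparator, and the mean symptom scores and birth data fill only part of the gap

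*Protocol article*

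**What the plan says.** All of this comes from the protocol article.

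- **Registration of harms** (Scientific ethical considerations): "Any side effects related to the intervention will be registered and published with the results of the study".
- **Handling of adverse events** (same section): "If any adverse events should occur, the teacher has the relevant expertise to ensure participant safety or referral to relevant treatment elsewhere". The section does not say who registers events or who decides on relatedness.
- **Safety background** (same section): "Participation in a mindfulness-based program has not been associated with an increased incidence of harm when compared to no treatment". The section names anxiety, traumatic re-experiencing and emotional sensitivity as the usual unwanted effects, and adds that "childhood adversity has been associated with a higher frequency of adverse effects".
- **Population** (Setting): the vulnerabilities that lead to referral include "a history of childhood adversity, sexual assaults, present physical or psychological intimate partner violence". The exclusion criteria under Recruitment and consent do not remove women with such histories.
- **Blinding**: "Group allocation will not be blinded since keeping participants blind to this type of intervention would not be possible".
- **Control arm** (Design): waitlist women are offered an equivalent programme once follow-up is over.
- **Data held in both arms** (Outcomes, Table 2; Participant characteristics): WHO-5 at T0 to T4; EDS and DASS-21 at T0, T2, T3 and T4; time and mode of delivery, birth length and weight from medical records.

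**The concern.** A side effect related to the intervention can hardly arise in a woman who has not yet been offered it. Followed as worded, the rule therefore yields a list from one arm. The effects that the article expects are also ones that women referred for mental disorder, abuse or partner violence may plausibly have without any mindfulness training. A one-arm list cannot separate such background events from effects of the programme. It could blame the programme for events that would have happened anyway, or leave out real harm that was put down to the woman's history. Open allocation makes that attribution more fragile.

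The article itself flags part of its population as being at higher risk, and says that the adapted programme still needs its own evidence base. The published harms result is therefore worth making interpretable.

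**Working it through.** **1. Figures in the plan.** The article gives no adverse-event rate and no harms precision, so there is no harms figure to reproduce. Its one related figure is the power. With 84 per arm (168/2) and SD 15.6, the standard error of the difference is 15.6 × √(2/84) = 2.407.
- Difference of 7: 7/2.407 − 1.96 = 0.948, power 82.8% (stated 82%).
- Difference of 8: 8/2.407 − 1.96 = 1.364, power 91.4% (stated 91%).

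Both reproduce, and nothing in this point affects them.

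**2. What the stated rule allows.** Registration requires relatedness, and exposure in the waitlist arm begins after follow-up. The expected waitlist count is therefore close to zero by construction, not because harm is absent. One arm gives a rate but no difference. For example, if none of 120 MBSR women had a registered event, the exact upper 95% limit would be 1 − 0.025^(1/120) = 3.0%, with no control figure to set beside it.

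**3. What the both-arm data cover.** Taking a month as 52/12 weeks:

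| Item | Weeks after randomization |
|---|---|
| Programme (starts at +2 weeks, lasts 9 weeks) | 2 to 11 |
| T1 (1½ months) | 6.5 |
| WHO-5 recall at T1 (14 days) | 4.5 to 6.5 |
| T2 (3 months) | 13 |
| DASS-21 and EDS recall at T2 (7 days) | 12 to 13 |

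On the stated timetable, no DASS-21 or EDS recall window falls inside the programme. It would have to run more than a week late before the T2 window reached it. WHO-5 is collected at T1, but the primary model under Statistical analysis plan lists only baseline, 3, 6 and 9 months.

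No scale in Table 2 is aimed at traumatic re-experiencing. The planned models compare means, and an average improvement can coexist with a minority who get worse.

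**4. What a both-arm comparison would give.** Assume equal event rates p in the two arms. The 95% half-width is 1.96 × √(2p(1 − p)/n):

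| Assumed p | n = 120 per arm | n = 84 per arm |
|---|---|---|
| 5% | ±5.5 points | ±6.6 points |
| 10% | ±7.6 | ±9.1 |
| 20% | ±10.1 | ±12.1 |
| 30% | ±11.6 | ±13.9 |

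For 80% power with 120 per arm, a 5% control rate would have to rise to about 16.1%, and a 30% rate to about 47.6%. Power to detect a doubling from 5% is 31%. This supports estimation and description, not a powered safety test.

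**The case against.** The strongest reply is that one sentence of a condensed article is being read as a complete collection rule. The sentence promises to register and publish related side effects. It does not say that other events go unrecorded, and the same section speaks separately of adverse events in general. Definitions, solicitation and causality procedures usually sit in the full protocol, which is not shown. This stands: the absence of those details is not the point here. The point is the condition that the article does state.

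A reader might go further and infer that the trial cannot say whether MBSR raises or lowers harm. The article does not support that. Anxiety, the first harm it names, is measured by DASS-21 in both arms and analysed with models equivalent to the primary one. Depression, stress and wellbeing are also compared, and birth data come from records. A lasting mean worsening would be visible by arm. For missing scores, the sensitivity analyses include a case in which MBSR outcomes are shifted downwards.

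A reader might also infer that the teacher judges relatedness. The article gives the teacher responsibility for safety and referral, and says nothing about who makes that judgement.

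Finally, both-arm event data would be imprecise, and recruitment began in March 2022, so new items would not cover every woman. Both are true. They limit the gain but do not give the one-arm list a comparator.

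**Conclusion.** The point holds in a limited form. As worded, registered harms lack a control-arm comparator in an open-label trial whose population the article itself regards as partly at higher risk. The remaining between-arm evidence, mean symptom scores and birth data, leaves three gaps: event-type harms such as re-experiencing, deterioration in individual women, and transient distress while the programme is running.

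The conclusion rests on the Table 1 timetable being kept and on the full protocol not already providing for both-arm collection regardless of cause. If it does, citing that provision settles the first part. The size of any harm cannot be stated, because the article gives no event rates; the 5% to 30% range is assumed. The primary estimate, its analysis and the power are unaffected.

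**What to change.** 1. Reword the rule so that the same short set of unwanted-effects items goes to both arms in REDCap at T1, T2, T3 and T4. T1 matters most, as the only assessment within the programme. Record answers whatever the suspected cause, with relatedness as a second field.
2. Report these events by arm, descriptively, with confidence intervals.
3. From data already collected, report by arm the number of women who worsen from baseline by a prespecified amount on WHO-5 (including T1), EDS and each DASS-21 subscale, with the number missing shown beside it. Fix the amounts before outcomes are examined by arm.

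**Cost.** A few questionnaire items, partly overlapping DASS-21 anxiety from T2 on, and an extra table or two. Women already past a visit cannot answer the new items for it, so the report should say how many per arm were asked. The deterioration table will not cover everyone either: 30% of 240, or 72 women, are expected not to complete, and those who leave because of distress may be among them.
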